### Inclusion and non-inclusion criteria

Inclusion and non-inclusion criteria are summarized in Table 2.

**Table 2 Tab2:** Inclusion and non-inclusion criteria

Inclusion criteria	Non-inclusion criteria
Being over 18 years old	Being treated with an antidepressant agent during the four weeks before inclusion
Suffering from an advanced cancer	Having had a hypersensivity event to mirtazapine, escitalopram of any excipient
Having a clinically estimated life expectancy over 3 months	Having had a prior inefficient treatment with mirtazapine or escitalopram
	Having postural hypotension or arterial systolic hypotension inferior to 90 mmHg measured following the guidelines of the European Society of Cardiology
Being diagnosed from having a depressive syndrome by a Hospital Anxiety and Depression Scale-D over 11	Having a QT interval over 420 ms
	Having uncontrolled heart rhythm disorder or uncontrolled conduction disorder
Being in need of an antidepressant treatment	Having had or having bipolar disorder
Suffering from at least one under-controlled symptom (defined as a score over 3 on the Edmonton Symptom Assessment Scale) among: pain, nausea, vomiting, breathlessness, lack of appetite, sleep disorders, or anxiety	Having uncontrolled seizure or epilepsy (relative non-inclusion criteria needing a neurology specialist opinion)
	Having or having a history of closed-angle glaucoma
Having or not a cancer treatment	Having bone marrow aplasia
Being able to understand the information related to the study, and to sign informed consent	Practicing breastfeeding or being pregnant
Having agreed to take part in the study	Women of childbearing age with no contraception method

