### Study procedure

#### Recruitment and inclusion procedure

A screening for potential participants will be made by clinical teams in oncology or palliative care, during consultations, day hospital or conventional hospitalization. The principal investigator will be informed of every potential participant. He will verify inclusion and non-inclusion criteria. If the potential participant fulfils all requirements, the principal investigator will meet the patient to give information about the study (and about the qualitative part of it if needed).

Then the participant will be called at least 48 h after having received the oral and written information. They will be asked if they want to part to the study. If positive, an appointment for inclusion, randomization and baseline assessment will be booked. At inclusion, participants will sign an informed consent to participate. For those who will take part in the qualitative part, they will receive separate information and sign a specific consent form.

At inclusion, participants will be clinically examined with a postural hypotension test and an ECG if no prior ECG is available. If the participant does not have any non-inclusion criteria, he will be enrolled in the study and receive an anonymity code generated by the ENNOV Clinical software. Socio-demographic data will be collected. The participant will have to fulfil the EORTC QLQ-C30, Hospital Anxiety and Depression Scale –Depression (HADS-D), Edmonton Symptom Assessment Scale 12 French (ESAS-12F), and Antidepressive Side-Effect Checklist (ASEC) questionnaires. The principal investigator will fulfil the MADRS questionnaire and assess the patient’s Performance Status. If needed, the principal investigator will be able to ask for a psychiatric opinion.

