#### Intervention and comparator

Mirtazapine will be compared to another antidepressant drug to avoid confusion bias in improving health-related quality of life due to the lone antidepressant effect of mirtazapine. Escitalopram has been chosen as a comparator because it is, like mirtazapine, effective in treating depression in advanced cancer [16], with few medication interactions [17], but no effect on poly-symptomatology is expected.

Both drugs will be used following the usual practice for depression. They will be introduced at a low dose regularly increase at day 7, 14 and 28 depending on the expected benefits from a higher dose and potential dose-dependent side effects. (Table 3).

**Table 3 Tab3:** Doses escalation during the study follow up

		**Starting doses – Day 0**	**Day 7**	**Day 14**	**Day 28**
		Mirtazapine: 15 mg Escitalopram: 10 mg (or 5 mg for patients older than 65)			
Excessive drowsiness (CTCAE grade 1 or rated moderate or severe using the ASEC)			*For patients under 65 in the escitalopram arm: decrease to 5 mg*		
			*For every other patients: Stop the treatment*		
Any severe adverse effect or serious adverse event (CTCAE grade > 3 or rated severe using the l’ASEC)			*Stop the treatment*		
Moderate adverse event (CTCAE grade 2 or rated moderate using the ASEC)			Decrease the dosage (Or treatment stop if already at the lower dosage)		
Mild adverse event (CTCAE grade 1 or rated mild using the ASEC)			No dose adjustment		
No adverse event	Inadequate symptoms’ control (ESAS > 3)		No dose adjustment (or increase the dosage if escitalopram has been started at 5 mg)	Increase the dosage	
	Adequate symptoms’ control (ESAS ≤ 3)		No dose adjustment		

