The proportion of patients having an improvement in the different EORCT-QLQ-C30 functioning scales will be compared between baseline, day 28 and day 56. The following cut-offs will be used for defining significant changes: 3 points for the Cognitive Functioning, 2 points for the Physical functioning, and 6 points for the Emotional Functioning and Role functioning [26, 27]. Financial functioning will not be assessed as the French health care system does not fit with this evaluation (cancer care is free of charge to the patient).

Weight variations will be assessed between baseline, day 28 and day 56.

The use of painkillers will be assessed using the proportion of patients that had stable (± 20%) morphine oral equivalent between baseline, day 28 and day 56. For other symptomatic treatments, the proportion of patients that increased the doses (or had new symptomatic treatment) between baseline, day 28 and day 56 will be assessed.

The security of use will be assessed using the number of new adverse effects reported using the ASEC on day 14, 28 and 56 and compared with baseline. Adverse events will also be recorded and graded using the CTCAE V4.0. The ESAS12-F subscales for drowsiness, fatigue and constipation will be used to compare these symptoms between baseline, day 28 and day 56. A higher degree of intensity will be considered from a 1 point difference [23].

Finally, adherence to medication will be assed using the MARS and Proportion for Days Covered at day 56 [28].

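### The ASEC safety outcome counts only new side effects, so worsening of a complaint already present at baseline is left out although ASEC severity is collected

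*Protocol article*

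**What the plan says.** The Outcomes assessment section of the protocol article lists three safety measures together and calls none of them main or primary.

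1. The ASEC count: "The security of use will be assessed using the number of new adverse effects reported using the ASEC", at days 14, 28 and 56. The sentence adds that the comparison is with baseline. It does not define what makes an effect new.
2. Graded events: "Adverse events will also be recorded and graded using the CTCAE V4.0".
3. Three symptom scales: "The ESAS12-F subscales for drowsiness, fatigue and constipation will be used to compare these symptoms between baseline, day 28 and day 56", with the rule "A higher degree of intensity will be considered from a 1 point difference".

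The ASEC is completed at inclusion: the Recruitment and inclusion procedure section ends its list of baseline forms with "and Antidepressive Side-Effect Checklist (ASEC) questionnaires". Table 1 schedules it again at days 7, 14, 28 and 56. It carries severity, since Table 3 classes effects by mild, moderate or severe ASEC rating, for example "Moderate adverse event (CTCAE grade 2 or rated moderate using the ASEC". Table 2 requires a symptomatic population: "Suffering from at least one under-controlled symptom (defined as a score over 3 on the Edmonton Symptom Assessment Scale", with a depressive syndrome as well. Cancer treatment may be ongoing.

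**The concern.** A count of new effects suits patients who start with few complaints. Here everyone has advanced cancer, depression and at least one poorly controlled symptom, so many may report something on the ASEC before taking any study drug. On the plain wording, each such item is removed from that patient's later count, however severe it becomes.

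The trial acts on ASEC severity elsewhere: under Table 3 a rating can lead to a dose change or to stopping the drug. The same rating, reached from a milder baseline complaint, would not register in this outcome. The third safety measure also treats a rise in intensity as harm, so the authors recognise worsening in principle but do not apply it to the ASEC.

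What is at stake is how completely the patient-reported side-effect comparison describes tolerability. The Discussion expects mirtazapine to be well tolerated, and this outcome will be read as evidence for or against that.

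**Working it through.** **No figure to reproduce.** The plan gives no number for any safety outcome. Its sample-size figures (167 per group, 418 in total) belong to the Global Health Status outcome and are not used here.

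**Which safety measure would register each event, as worded**

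| Event | ASEC count | CTCAE record | ESAS12-F safety items |
|---|---|---|---|
| Effect absent at inclusion, present later | Yes | Yes, if recorded | Drowsiness, fatigue, constipation only |
| Effect mild at inclusion, severe later | No | Yes, if recorded as an event | Drowsiness, fatigue, constipation only |

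The secondary efficacy outcomes also follow pain, nausea, vomiting, appetite, breathlessness, sleep, anxiety and mood on the ESAS-12F. They are framed as improvement, and the per-patient proportion counts only symptoms that became less intense, so an unchanged symptom and a worse one score alike.

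**How much the new-only count could miss.** The rates below are assumptions, because the documents give none.

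- b = share of ASEC items present at baseline
- e = chance that an absent item appears
- w = chance that a present item worsens

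Per item, new effects are (1 − b)e and worsened effects are bw. The number of items cancels, so

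share missed = bw / [(1 − b)e + bw].

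| b | e = 10%, w = 10% | e = 10%, w = 20% |
|---|---|---|
| 10% | 0.01 / (0.09 + 0.01) = 10% | 0.02 / (0.09 + 0.02) = 18% |
| 30% | 0.03 / (0.07 + 0.03) = 30% | 0.06 / (0.07 + 0.06) = 46% |
| 50% | 0.05 / (0.05 + 0.05) = 50% | 0.10 / (0.05 + 0.10) = 67% |

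When e = w the formula reduces to b. If worsening is rarer than onset, the loss is smaller: with w at half of e (5%) and b = 30%, it is 0.015 / (0.07 + 0.015) = 18%.

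**Effect on the comparison between arms.** Suppose that within each arm e = w = p, and that b is the same in both arms, as randomisation gives on average. Each arm's new-only rate is then (1 − b)p. The difference between arms shrinks by the factor (1 − b), to 70% of its size at b = 30%. The ratio between arms does not change.

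**The case against.** **The ASEC count is not the only safety measure, and nothing calls it the main one.** This stands. A reader might infer that a mild complaint turning severe counts as no harm at all in this trial. The documents do not support that. Table 1 has a separate side-effects row at every contact from inclusion on, and the Follow-up procedure section sends events found at the telephone calls for a clinical opinion. Table 3 sets severe ASEC ratings beside CTCAE grades. A patient stopped for such an effect should therefore appear in the graded record. The answer is only partial: the article gives no rule for recording a worsened baseline complaint as a CTCAE event, and states no comparison of CTCAE events between arms. The trial is open-label, so whoever records the event may know the treatment. Patients completing the ASEC know it too, but the checklist is put to everyone at fixed contacts and can be set against each patient's own baseline.

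**Other symptoms are tracked by intensity.** This also stands in part, since the ESAS-12F efficacy outcomes would hold the data. They are not defined to detect harm.

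**A reader might infer a specific loss of power.** The documents do not support one. They give no prevalence or event rates and make no power claim for safety. A calculation for one yes/no item would also not model a count over a checklist. Under the simple assumptions above the relative effect is preserved, so the fault is lost information and a smaller absolute difference rather than a distorted ratio.

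**The full protocol or SAP may define new effects to include worsening.** It may, and neither is shown. The published wording nevertheless states a rule, and its ordinary meaning excludes worsening.

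**Conclusion.** The point holds for the ASEC outcome, not for the safety assessment as a whole. As worded, the ASEC count ignores worsening of effects present at inclusion, in a population selected for being symptomatic and with severity ratings that the trial collects and uses. CTCAE grading and the three ESAS12-F items cover part of this. For other ASEC effects, the capture of worsening as harm rests mainly on CTCAE recording in an open-label trial.

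The size cannot be fixed from the documents. Across the assumed scenarios with worsening as frequent as onset or twice as frequent, the new-only count misses between 10% and 67% of new-or-worsened items, and less where worsening is rarer than onset. The article does not list the ASEC items, so how far they overlap with the entry symptoms is also unknown. The conclusion assumes that the word new carries its ordinary meaning and that the baseline ASEC records severity as Table 3 implies. The point does not touch the primary outcome, and it is worth correcting because the correction is cheap.

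**What to change.** In Outcomes assessment, define the ASEC safety outcome as the number of effects that, at any post-baseline contact, are either absent at inclusion and now present, or rated at least one ASEC severity grade above that patient's own inclusion rating. Report the new-only count beside it as supportive. Counting any post-baseline contact also brings in day 7, when the ASEC is scheduled and from which the safety objective runs, but which the current outcome omits.

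If the full protocol or SAP already defines new effects to include worsening, say so in the outcome wording. If the new-only count is kept as it is, state that worsening is to be read from the CTCAE grades and the ESAS12-F, and give the rule for recording a worsened baseline complaint as an event.

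The cost is wording only, since the ASEC is already scheduled at inclusion and at every later contact. The downside is that counts will rise in both arms and will include worsening from disease progression or cancer treatment. Randomisation balances that between arms on average but it adds noise. The new-only count has a similar weakness, because progression also produces new complaints.

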### Objectives

The primary objective will be to assess the effectiveness of oral mirtazapine in improving HRQoL in poly-symptomatic advanced cancer patients suffering from depression after 56 days of treatment, compared with oral escitalopram.

The secondary objectives are:

i- To assess the effectiveness of oral mirtazapine in poly-symptomatic advanced cancer patients suffering from depression compared with escitalopram on the following outcomes:The experience of poly-symptomatology, poly-medication, and taking antidepressant agents and explore the dynamic of this experience between inclusion and 56 days.The improvement of the following symptom intensity: depressive mood, pain, nausea, lack of appetite, vomiting, breathlessness, sleep disorders and anxiety at 28 and 56 days.The improvement of the different functional capacities at 56 days.The mitigation of the loss of weight at 28 and 56 days.The use of medications to treat associated symptoms at 28 and 56 days.

ii- To assess the safety of oral mirtazapine in poly-symptomatic advanced cancer patients suffering from depression compared with escitalopram from 7 days.

iii- To assess the compliance to the treatments.

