#### Follow-up procedure

Follow-up will be made on a regular basis during a 56-day period.

Patients will be called by a research assistant on days 7 and 14 to screen for side effects using the ASEC scale. If any adverse event is screened a clinical opinion will be sought for dose adaptation based on predefined criteria. On day 14, escalation of dose will be prescribed by the PI if symptoms are still under controlled (the corresponding ESAS12-F subscale rated over 3) and in the absence of limiting side effect evaluated using the ASEC and Common Terminology Criteria for Adverse Events V4.0.

Clinical assessment will occur on day 28 (more or less 3 days). This assessment is meant to be made physically; however, if the patients’ condition of public-health situation demands it, it will be performed using teleconsultation. During this consultation, the patient will fulfil the EORTC QLQ-C30, ESAS -12F, HADS-D, and ASEC questionnaires. The PI will weigh the participant, count the number of pills that remains to the patient, evaluate the Performance Status and fill the MARDS. Considering all available data (tolerance, side-effects and symptom control), the PI will make the decision regarding the escalation of treatment dose.

During the final evaluation, on day 56, the patient will fulfil the EORTC QLQ-C30, ESAS -12F, HADS-D, ASEC, and factor 1 of the Medication Adherence Rating Scale (MARS) questionnaires. The PI will weigh the participant, count the number of pills that remains to the patient, evaluate the Performance Status and fill the MADRS.

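### The ASEC safety count leaves out day 7, although the safety objective starts there, the ASEC is collected then, and treatment can first be stopped or reduced then

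*Protocol article*

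**What the plan says.** All references are to the protocol article.

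- **Objectives, item ii:** "To assess the safety of oral mirtazapine in poly-symptomatic advanced cancer patients suffering from depression compared with escitalopram from 7 days".
- **Table 1:** the ASEC is marked at inclusion and on days 7, 14, 28 and 56. A separate side-effects row is marked at the same times.
- **Follow-up procedure:** "Patients will be called by a research assistant on days 7 and 14 to screen for side effects using the ASEC scale". If an adverse event is found, a clinical opinion on the dose follows.
- **Intervention and comparator, Table 3:** ASEC and CTCAE ratings lead to dose action from the Day 7 column onward. For example, the row "Moderate adverse event (CTCAE grade 2 or rated moderate using the ASEC") carries the action "Decrease the dosage (Or treatment stop if already at the lower dosage"). Severe effects lead to a stop. Excessive drowsiness leads to a reduction or a stop, depending on arm and age.
- **Outcomes assessment:** "The security of use will be assessed using the number of new adverse effects reported using the ASEC on day 14, 28 and 56", compared with baseline. The next sentences add CTCAE V4.0 recording and grading, with no visits named, and a comparison of the ESAS12-F drowsiness, fatigue and constipation subscales between baseline, day 28 and day 56.

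**The concern.** The outcome definition names its days, and the list disagrees with the objective it serves and with the visit schedule. No reason is given for dropping day 7. This is not detail left to an unseen analysis plan: the article states a rule, and the rule conflicts with its own text.

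The omitted visit is the first ASEC after treatment starts and the first at which the protocol can act on poor tolerance. If a drug is stopped or reduced on day 7 and the effect then fades, the day-14 ASEC may no longer show it. The ASEC count would then describe tolerability only after the protocol has responded to early intolerance. The Discussion expects mirtazapine to be well tolerated, so early tolerability bears on a conclusion that the trial intends to draw.

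**Working it through.** The document gives no figure for this outcome, so there is none to reproduce. The check sets the passages side by side.

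**1. Days collected and days counted**

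| ASEC day | Collected (Table 1) | Within the safety objective | Table 3 action possible | In the ASEC outcome |
|---|---|---|---|---|
| 0 | yes | baseline | no | reference |
| 7 | yes | yes | yes (first time) | **no** |
| 14 | yes | yes | yes | yes |
| 28 | yes | yes | yes | yes |
| 56 | yes | yes | – | yes |

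Four post-baseline assessments are collected and three are counted. The share left out is 1/4 = 25% of assessments. That is a share of visits, not of events.

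**2. Which effects fall outside the count**

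Take an effect absent at baseline and write 1 or 0 for reported or not on days 7, 14, 28 and 56. There are 2^4 − 1 = 15 patterns with at least one report.

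- If the count is over any listed visit, an effect is missed only when days 14, 28 and 56 are all 0 and day 7 is 1. That is one pattern of 15: (1,0,0,0). An effect that persists or returns is still counted.
- If the count is per visit, the day-7 figure is absent altogether.

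On either reading, the transient day-7 effect is left out. The number of patterns says nothing about how often each occurs.

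**3. Whether another measure covers the gap**

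- CTCAE recording: yes in principle, as no visits are named and Table 1 has side effects on day 7.
- ESAS12-F drowsiness, fatigue and constipation: no. Table 1 collects the scale at baseline, day 28 and day 56 only.

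No other patient-reported measure therefore covers day 7. The ASEC is also the only safety measure in that section defined as a number of new effects against baseline.

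**4. Effect on the comparison between arms**

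Let t_M and t_E be the mean number of day-7-only new effects per patient on mirtazapine and escitalopram. On the any-visit reading:

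difference with day 7 = difference as defined + (t_M − t_E)

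The omitted term may be positive, zero or negative. The document gives neither t_M nor t_E, nor the ASEC recall period. A recall period reaching back past day 7 would shrink both terms.

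**The case against.** The strongest reply is that nothing important is lost. Adverse events are also recorded and CTCAE-graded without limit to particular visits, side effects are recorded on day 7, and a day-7 finding prompts a clinical opinion. An effect serious enough to change treatment is the kind most likely to be captured that way. Effects lasting to day 14 stay in the ASEC count. This stands, and it confines the point to the ASEC count. It does not reconcile the listed days with the objective and schedule. Outcomes assessment also says that outcomes rest mainly on patient report, and the ASEC is the safety measure it names first.

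A reader might infer three stronger things that the document does not support.

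- **That the omission favours mirtazapine.** Table 3 stops mirtazapine patients for excessive drowsiness, while escitalopram patients under 65 are reduced. But the remaining escitalopram patients are stopped too, no age distribution is given, and a reduction can also make an effect fade. The action differs by arm, so the loss may differ. Its direction is not established.
- **That a size can be attached.** Assumed day-7-only rates of 20% and 10% would hide 0.10 × 209 = 20.9, about 21 patients, with 418/2 = 209 per arm. Equal rates hide no difference, and reversed rates turn the sign. None of these rates comes from the document.
- **That patients stopped at day 7 leave the comparison.** The Statistics section specifies intention to treat on all included patients, and nothing says that stopping treatment ends ASEC follow-up.

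**Conclusion.** The inconsistency is certain: the ASEC outcome omits day 7, contrary to the objective, Table 1 and the Follow-up procedure. One of four post-baseline assessments is unused, and it is the first at which Table 3 can stop or reduce treatment. New effects reported on day 7 and not on day 14 or later are outside the ASEC count and appear only through CTCAE or side-effect recording.

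The size and direction of any distortion between arms cannot be computed from the document. The practical consequence rests on two assumptions: that some new effects are reported on day 7 and resolve by day 14, and that the day-14 ASEC does not ask back far enough to recover them. This affects one component of a secondary safety outcome. It does not touch the primary analysis. It is still worth correcting, because the written rule drops early transient effects from the one safety measure explicitly counted against baseline.

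**What to change.** In Outcomes assessment, add day 7 to the listed days, so that the outcome is the number of new ASEC adverse effects against baseline on day 7, 14, 28 or 56. State that patients who stopped treatment at day 7 are included. The section then agrees with the safety objective, Table 1 and the Follow-up procedure.

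The cost is one phrase. The day-7 ASEC is already collected, so there is no added burden on patients or centres, and no dose or stopping rule changes. The change should be made before any safety data are compared by arm: the trial is open-label, and a later choice about whether day 7 counts would be open to challenge.
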